| This is a prospective pilot randomised trial to study the effectiveness of prednisolone versus methotrexate in achieving clinical or radiological complete response for women with IGM. The study will be conducted in NUH. This study evaluates the effectiveness of each drug in terms of clinical and/or radiological response, time to resolution as well as total number of flares over a period of one year follow-up. This study can potentially identify a more effective treatment with fewer side effects for women with IGM as well as personalize drug choices for patients who are at risk of frequent flares. |  |
| **HYPOTHESIS AND OBJECTIVES** |  |
| Hypothesis |  |
| The hypothesis is that methotrexate has a higher 6-month clinical or radiologically complete response with lesser side effects than prednisolone. The time to clinical or radiological response is shorter in the methotrexate arm compared to prednisolone arm. Relapse and time to first relapse is lower and longer in the methotrexate arm compared to prednisolone arm. |  |
| Primary Objectives |  |
| The primary objective is to evaluate the 1) Proportion of patients who achieved clinical or radiological complete response at 6 months 2) Time to clinical response and time to radiological response, and 3) Proportion of patients with relapse in one year within affected breast between each arm. |  |
| Secondary Objectives |  |
| The secondary objectives include evaluation of:   1. Side effects 2. Frequency of percutaneous or surgical intervention required 3. Potential biomarkers that may predict response to treatment: eg IL-6, CRP and neutrophil to lymphocyte ratio (NLR) 4. Patient reported outcome measures 5. Validate survey instrument for IGM patients |  |
| Potential Risks and benefits |  |
| End Points – Efficacy |  |
| Benefits expected for the patient are the total remission of IGM or reduced relapsed/flare of IGM. |  |
| End Points – Safety |  |

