| Figure 1 below shows the study timeline for prednisolone and methrotexate treatment arm.  Figure 2 shows the drug dosage and schedule.  **Figure 1: Study Timeline for Prednisolone and Methotrexate Treatment Arm**   \| **Prednisolone/Methotrexate** \| \| **Study period (1 year)** \| \| \| \| \| \| \| \| --- \| --- \| --- \| --- \| --- \| --- \| --- \| --- \| --- \| \| **Phases** \| \| **Screening** \| **Treatment phase** \| \| \| \| **Follow-up phase** \| \| \| **Time point** \| \| Baseline \| T_0_ \| T_1_ \| T_2_ \| T_3_ \| T_4_ \| T_5_ \| \| Day 0 \| 1^st^  Month \| 2^nd^  Month \| 3^rd^  Month \| 6^th^  Month \| 12^th^  month \| \| Assessment \| Window Period (Day) \|  \| ±7 \| ±14 \| ±14 \| ±14 \| ±14 \| ±30 \| \| Clinical Visit \| X \| X \| X \| X \| X \| X \| X \| \| Blood Test for  FBC/LFT/RP \| X \|  \| X \| X \| X \| X \|  \| \| Blood Test for  Anti-HBc/Anti-HCV/HBsAg/ Serum Beta-HCG pregnancy test ^1^ \| X \|  \|  \|  \|  \|  \|  \| \| Additional Blood for Research \| X \|  \| X \|  \|  \| X \|  \| \| Chest X-Ray ^2^ \| X \|  \|  \|  \|  \|  \|  \| \| Starting Dose \|  \| X \|  \|  \|  \|  \|  \| \| Dose Assessment \|  \|  \| X \| X \| O \|  \|  \| \| Breast Ultrasound \|  \|  \|  \|  \| X \| O \|  \| \| Surveys \|  \| X \|  \|  \|  \|  \| X \|   X= compulsory procedure O=procedure depending on the doctor’s discretion   1. Blood tests (Anti-HBc/Anti-HCV/HBsAg) will be exempted if patient has done the same test within 30 days. 2. Chest X-Ray will be exempted if patient has done the same test within 30 days.   **Figure 2: Flowchart of the treatment schedule for prednisolone and methotrexate during the treatment phase.**  [figure not shown] |  |
| **STUDY DESIGN** |  |
| Summary of Study Design |  |

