| *Screening*  After patient is consented to the study, a baseline blood test (32mls, including pregnancy test, Hepatitis B test, Hepatitis C test, full blood count, liver function test and renal function test) and chest X-Ray will be conducted during the baseline visit to assess for eligibility prior to enrolment to the treatment phase. Additional research blood (14.5mls, 1 tablespoons) will be collected at this baseline visit for research purposes. Patient may be exempted from chest X-Ray and/or blood test if patient has done the same test within 30 days.  Baseline demographics and relevant clinical variables of patients will be collected. The following demographic and clinical variables will be collected: age of presentation, pre-menopausal or post-menopausal status, parity / breastfeeding status, concomitant rheumatic conditions, personal or family history of tuberculosis, smoking or alcohol intake, presenting complaint, unilateral or bilateral involvement, affected quadrant of the breast, duration of symptoms and previous antibiotics prescription for treatment of IGM.  Information on comorbidities will be evaluated to ensure suitability for both treatment arms prior to recruitment. Examples include drug allergies, plans for pregnancy, ongoing infection, previous history of cancer, previous tuberculosis, epilepsy, diabetes, hypertension, kidney, liver, cardiac problems, osteoporosis, glaucoma, peptic ulcers, previous side effects to either prednisolone or methotrexate.  If patient fulfilled all the eligibility criteria after screening assessment, she will be randomised to either of the treatment arm.  If patient did not meet the full eligibility criteria (eg. Pregnant, hepatitis carrier or abnormalities in renal or liver panels), she will not proceed to the treatment phase. The data collected and additional blood samples will be kept for analysis.  *Treatment Phase*  Patient will be scheduled to attend a clinical visit (T_0_) to either breast or rheumatology clinic if she meets all eligibility criteria for the initiation of treatment dose. There will be a window period of ± 7 days for this clinical visit. Patient is required to complete a pre-treatment quality of life online survey (approximately 10-15 minutes).  Patient will be scheduled for blood test (8mls, 0.5 tablespoons) and clinical visits to either breast or rheumatology clinic at the 1^st^ (T_1_), 2^nd^ (T_2_), 3^rd^ (T_3_) and 6^th^ (T_4_) month to assess their signs and symptoms, and drug compliance. There will be a window period of ± 14 days for each of these clinical visits. Additional research blood (14.5mls, 1 tablespoons) will be collected on the 1^st^ (T_1_) and 6^th^ (T_4_) months.  Patients are required to undergo a breast ultrasound to assess for their radiological response during the 3^rd^ (T_3_) clinical visit. A window period of ± 14 days will be applicable. The initial measurement of the breast lesion or mass will be recorded in three dimensions – i.e. anteroposterior, superior-inferior, mediolateral measurements. If complete clinical and radiological complete response has been achieved on the 3^rd^ (T_3_) visit, the doctor will discontinue the drug in a safe manner and no further breast ultrasounds will be required. If the patient’s symptoms or signs have not resolved by the 3^rd^ (T_3_) clinical visit, patient’s drug dosage will be assessed by the rheumatologist and treatment may be continued up to the 6^th^ (T_4_) month period and a repeat breast ultrasound will be required at the 6^th^ (T_4_) month. If symptoms have not resolved by the 6^th^ (T_4_) month of clinical visit, the patient’s drug dosage may be up-titrated or will be given an addition of a second therapy, i.e. combination therapy of steroid and methotrexate may be used. For clinical visits mention above, it will coincides with standard care visit.  During the clinical visits, Tingting Hu et al’s “M- score” will be adopted to grade the severity of the disease. M score is being calculated during clinical visits for IGM patients regardless of trial status for objective follow up. This is a common practice. For this study, the score will be administered by their attending healthcare professional (not limited to breast surgeons, investigators, or breast care nurses).  The M-score will be the sum of the following:  1) Mass score  2) Erythema score  3) Fistula score  4) Pain score  5) Quality-of-life (QoL) score  The scoring criteria were defined as follows:  1) Mass score: 0 for the absence of mass by palpation; 1 for mass ≤3 cm by palpation; 2 for mass >3 cm by palpation.  2) Erythema score: 0 and 2 for the absence and presence of erythema, respectively  3) Fistula: 0 and 2 for the absence and presence of fistula, respectively  4) Pain Score: 0 for Visual Analogue Score (VAS) 0-2; 1 for VAS 3-5; 2 for VAS 6-10  5) QoL score: 0 for absence of effects on QoL; 1 for mild effects on QoL, where the patient does not require medical assistant; 2 for serious effects on QoL, where the patient requires medical assistant  The total M-score ranges between 0 and 10 and serves as a quantitative and objective measurement of the severity of the symptoms.  The primary endpoint will be the clinical complete response (cCR) rate, which is defined as the proportion of patients who have an M-score of ≤ 1 at ≤1 years after treatment.  The secondary endpoints will be as follows:   - - The time to cCR, defined as the median time to cCR post randomisation.   - The treatment failure (TF) rate, defined as the proportion of patients with TF at 1 year post randomisation. The TF status will be defined as follows:     - If the patient has an M-score ≥6 before randomisation, TF is defined as the M-score remaining at ≥6 at 1 month post randomisation.     - If the patient has an M-score between 4 and 5 before randomisation, TF is defined as the M-score remaining at ≥4 and never being lower than 4.     - If the patient has an M-score <4 at baseline but never reaches cCR after randomisation, TF is defined as the M-score being >5 at the follow-up and remaining above 5 for one month. - Relapse rate, which is defined as the proportion of patients who have M-score >4 among the patients who achieved CR.   Throughout the course of the study, there are possible flares and relapse of the disease. Flares will be defined as any increase in M-score or lesion size on ultrasound whilst on therapy. While relapse will be defined as recurrence of symptoms or signs of IGM in the breast after previously experiencing complete resolution following therapy. If relapse occurs, patient will restart the same treatment arm for 6 months.  In the event of flares, blood test (8mls, 0.5 tablespoons) and additional research blood (14.5mls, 1 tablespoons) will be collected and the allocated treatment for the patient will be up-titrated by the doctor. In event of relapse, treatment for the patient will be reinitiated as per the allocated arm.  Additional research blood samples collected during the trial will be used for gene expressing profiling to identify unique patterns of gene expression that can be used to diagnose IGM and predict its treatment response.  Regardless of treatment arm, patient will be monitored by either breast surgeon or rheumatologist. Surgeons will assess for eligibility into trial, clinical reviews, and ultrasound breasts interpretation. Rheumatologists will be monitoring for drug side effects and titration if required. In event of failure of medical therapy, surgeons will have to intervene accordingly for aspiration or surgical drainage. In the event where patients require aspiration or surgical drainage during the study, methotrexate or prednisolone should be continued unless there is evidence of sepsis. The frequency of aspiration or surgical intervention will be recorded as events during the study.  Whenever the disease has been resolved during the study period, the balance medication and/or packaging will be retrieved to do medication accounting and checking for adherence to assigned treatment arm.  If side effects were to develop, doctors will evaluate the severity of the side effects and withdraw the patients from the trial if needed. |  |

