| *Follow up Phase*  The last clinical visit at the 12^th^ (T_5_) month may be a physical clinical visit or teleconsultation, depending on the doctor’s decision. Patient will be asked to complete a post-treatment quality of life online survey (approximately 10-15 minutes) during this visit. There will be a window period of ± 30 days for the last clinic visit. Please refer to Figure 1 for the study timeline. |  |
| **iii. Post Study Follow up and Procedures** |  |
| If there are any unresolved adverse events that require medical intervention, follow-up visits will be conducted and verified through the electronic medical records of their hospitalisation.  In the case of serious adverse events, this will be reported to the DSRB as soon as possible, no later than 7 calendar days after first knowledge by the investigator, and any additional relevant information about the event should be reported within 8 calendar days of making the initial report.  Patients’ clinical information and personal data may be combined or linked with, including but not limited to: government administrative data and research data such as, nation-wide health-related databases, economic data and National Autoimmune Registry, up to 31 December 2043. The linkage may be carried out by itself or with the assistance of a data intermediary. The collection of such data is for the purposes of the current research study and will be collected prospectively. |  |
| **iv. Discontinuation Visit and Procedures** |  |
| A discontinuation visit will be conducted for all patients who discontinued the study drug or withdrawn from the study regardless of whether it is voluntary based on patient’s request or decided by the Investigators for safety or non-compliance issues to follow-up on:   - Balance medication and packaging retrieval to do medication accounting and checking for adherence to assigned treatment arm - Existing AE(s) /SAE or complaints that are not resolved and to ensure that care assessment with support care delivery is continued until the problem is resolved. - Reason for withdrawal (if requested by the patient) |  |
| **TRIAL MATERIALS** |  |
| Trial Product (s) The investigational product (IP) and Auxiliary Product (AP) will be procured locally from NUH pharmacy and stored at NUHS Investigational Medicine (IMU) facility. |  |

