| De-identified blood samples will be analysed and stored in NUH Tissue Repository. Recruitment and follow-up survey data will be collected electronically via NUHS REDCap. Only study team members with delegated rights will be able to access the data under the supervision of PI and Site-PI. All survey data will be collected electronically via FormSG. A copy of de-identified data will be stored in a secured server at NUH. |  |
|  |  |
| **SAMPLE SIZE AND STATISTICAL METHODS** |  |
| Determination of Sample Size |  |
| The prevalence rate of IGM in NUH is currently at 10 to 15 patients per year. Based on a stepped rule of thumb, a minimum sample size of 30 will provide at least 80% power to detect a medium standardised effect size of between 0.3 to 0.7 based on a randomised two-group comparison (Machin et al, 2021). Assuming a 20% attrition rate, the sample size required for this study is 36 patients. This will be rounded up to a sample size of 40 patients over a period of 36 months. |  |
| Statistical and Analytical Plans The primary outcome of 6-month clinical or radiological complete response will be compared between arms using Chi-square test. The effect estimate will be quantified in terms of difference in proportion as well as relative risk (RR) and their associated 95% confidence interval (CI). The secondary outcomes of time-to clinical or radiological response and time-to-relapse will be evaluated via the Kaplan-Meier method. The differences in survival curves will be compared using log rank test, with the effect estimate quantified in terms of hazard ratio and its 95% CI. The primary analysis of this trial will be based on Intention-to- Treat (ITT). A Per Protocol (PP) analysis will be performed on all patients who have completed 6 months of treatment regimen as a sensitivity analysis.  Chi square test will be used to evaluate the proportion of side effects and requirement for percutaneous or surgical intervention during treatment between arms. Modified Poisson regression will be used to identify clinical or biomarkers that are associated with treatment response and quantify the effect in terms of RR.  Patient reported outcomes will be reported via a survey on FormSG, conducted online. The questions will be adapted from SF36 V1 Singapore version and EORTC-BR23. Below are the domains to be compared:   - - General Health   - Physical Health   - Mental Health   - Body Image   - Sexual Image   - Breast Health |  |
| **ETHICAL CONSIDERATIONS** |  |

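### The ultrasound and visit schedule does not match the endpoints: conflicting month-6 scan rules, no dated reference scan, and a 12-month visit that may exclude palpation

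*Protocol*

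**What the plan says.** **Outcomes.** Section 11.2 states: "The primary outcome of 6-month clinical or radiological complete response will be compared between arms using Chi-square test". The primary objectives in section 2.2 also include "Time to clinical response and time to radiological response, and 3) Proportion of patients with relapse in one year within affected breast". Section 6.3 defines clinical complete response (cCR) as an M-score of 1 or less within one year, relapse as an M-score above 4 among patients who had responded, and flare as any rise in M-score or in ultrasound lesion size while on therapy.

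**Ultrasound.** The "Breast Ultrasound" row of Figure 1 (section 4) is blank at Baseline, T0, T1 and T2, has X at T3 (month 3) and O at T4 (month 6), and is blank at T5 (month 12). The key reads "O=procedure depending on the doctor’s discretion". Section 6.3 says: "Patients are required to undergo a breast ultrasound to assess for their radiological response during the 3^rd^ (T_3_) clinical visit". After clinical and radiological complete response at T3, "the doctor will discontinue the drug in a safe manner and no further breast ultrasounds will be required". If symptoms or signs persist at T3, the same section makes a repeat scan at T4 a requirement. It also mentions an initial three-dimensional lesion measurement, without giving a visit or a method.

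**Month 12.** Section 6.3 (Follow up Phase) says that the visit at the 12th "month may be a physical clinical visit or teleconsultation, depending on the doctor’s decision". The M-score criteria include "Mass score: 0 for the absence of mass by palpation; 1 for mass ≤3 cm by palpation; 2 for mass >3 cm by palpation".

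**Blinding.** Section 8.5 states that the trial is open label for patients and study team.

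**The concern.** When response can be met clinically or radiologically, a scan can only add responders. If a doctor who knows the arm decides who is scanned at month 6, the chance of meeting the outcome depends partly on that decision. Figure 1 and section 6.3 give different rules for the same scan, so a site can follow either and comply with the protocol.

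Growth on ultrasound cannot be judged without an earlier scan, and none is scheduled before month 3. At month 12 one component of the M-score cannot be obtained remotely, and the doctor chooses the format of the visit. T5 is also the only scheduled visit after month 6, so it carries the later part of one-year relapse, which is a primary objective. An analysis plan cannot recover measurements that were never scheduled.

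**Working it through.** The protocol gives no figure to reproduce here, so the check sets each endpoint against the schedule.

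**1. Who is scanned at T4, and does it matter?** Here "resolved" in the text rule is taken to mean clinical complete response.

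| State at T3 | Section 6.3 | Figure 1 | When a missing T4 scan matters |
| --- | --- | --- | --- |
| Clinical and radiological response | Waived | Discretionary | Only if symptoms return by T4 and the outcome means status at month 6 |
| Symptoms or signs unresolved | Required | Discretionary | If Figure 1 is followed and the patient is not in clinical response at T4 |
| Clinically resolved, scan not clear | No rule | Discretionary | If clinical response is lost by T4 and the outcome means status at month 6 |

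T4 is a compulsory clinic visit, so the clinical limb is observed in every patient who attends. If response means by month 6, rows 1 and 3 already count through the T3 result, and only row 2 depends on a T4 scan.

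**2. Size.**
- One reclassified patient in an arm of 20: 1/20 = 5 percentage points.
- Let c be the clinical response rate, r the radiological response rate among the other patients, and s1 and s2 the proportions of those other patients scanned in each arm. Between-arm bias = (s1 − s2) × (1 − c) × r.
- The protocol gives none of these rates. Assume c = 0.6 and r = 0.3 to 0.5. Then (1 − c) × r = 0.4 × 0.3 = 0.12 to 0.4 × 0.5 = 0.20.
- With s1 − s2 = 0.2, the bias is 0.2 × 0.12 = 0.024 to 0.2 × 0.20 = 0.04, that is 2.4 to 4 points, or 0.48 to 0.8 of a patient in 20.
- With s1 − s2 = 0, it is zero.
- The share with full response at T3 is not given either. At an assumed 20%, 40%, 60% or 75%, the text waives the T4 scan for 4, 8, 12 or 15 of 20 patients per arm. All of them are documented responders at T3.

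**3. Reference scan and timing.** Scheduled ultrasounds number 0 before T3, 1 for all patients at T3, 1 conditional at T4 and 0 at T5. An increase on ultrasound before T3 has no scheduled comparator. Time to radiological response can take only two scheduled values, about month 3 and about month 6.

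**4. M-score without palpation.** The other four items (erythema, fistula, pain, quality of life) carry 0-2 points each and sum to S, from 0 to 8. The total lies between S and S + 2.
- cCR (total ≤1): S = 0 gives 0-2 and S = 1 gives 1-3, both undetermined. S ≥2 excludes cCR.
- Relapse (total >4): S ≤2 gives at most 4, so relapse is excluded. S = 3 gives 3-5 and S = 4 gives 4-6, both undetermined. S ≥5 establishes relapse.
- Scoring an unpalpated mass as zero would classify S = 0-1 as cCR and S = 3-4 as no relapse. Both choices favour a good outcome.

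**The case against.** The strongest reply is that the gap is narrow. Section 6.3 does require the T4 scan for unresolved patients, and the O in Figure 1 can be read as shorthand for that conditional scan. The exempt patients are documented responders. Patients clinically resolved but not clear on scan meet the outcome clinically if they stay resolved. This stands, and it limits the effect to the patients identified in the table. It does not remove the problem, because the key to Figure 1 says discretion, not condition, and section 11.2 does not say whether response means at or by month 6.

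A reader might infer that month-6 radiological status is optional for every patient not in full response at T3. The text of section 6.3 does not support that. A reader might also take the 12 to 20 points above as the bias in the trial. That figure compares everyone scanned with no one scanned; a between-arm bias of that size would need one arm fully scanned and the other not at all.

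On the reference scan, an initial measurement is planned, absence of a lesion may need no baseline size, and flare also has an M-score limb. These points stand, but the ultrasound limb of flare still lacks a dated comparator.

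On month 12, cCR reached at T1-T4 already counts, treatment failure in patients with a baseline M-score of 6 or more is judged at 1 month, and many sums remain decisive. This also stands. A reader might infer that the teleconsultation undermines the 6-month outcome; it does not, because T4 is a clinic visit.

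**Conclusion.** The concern holds in limited form, as a mismatch that should be fixed.

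- **Month-6 scan:** the two rules contradict each other and one group has no text rule. The influence of an unblinded doctor is confined mainly to patients not in clinical response at T4 who are not scanned. Bias scales with the difference in scanning between arms: 2.4 to 4 points for a 20-point difference under the assumed rates, and nothing if scanning is equal. Each reclassified patient moves an arm by 5 points.
- **Reference scan:** the ultrasound part of flare has no scheduled comparator before month 3.
- **Month 12:** with mass unscored, cCR is undetermined at sums of 0-1 in patients without earlier cCR, and M-score relapse is undetermined at sums of 3-4. The outcome in section 11.2 is untouched.

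The documents do not show that ascertainment will differ by arm; they show that nothing prevents it. Nor do they make it necessary to replace the primary outcome or to drop time to radiological response.

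**What to change.** 1. Reconcile Figure 1 with section 6.3 so that the T4 ultrasound is compulsory for every patient without both clinical and radiological complete response at T3. This concerns the assessment only, not the decision on study drug.
2. Define the primary outcome as response by month 6, so that a documented T3 response counts.
3. Name the diagnostic ultrasound as the baseline reference where one exists (an assumption, since the protocol does not mention it), and record its date and measurements.
4. Analyse time to radiological response as grouped or interval-censored data with assessments at months 3 and 6, or report it as proportions at those times.
5. Require the T5 M-score in person. Where only a teleconsultation takes place, do not score mass as zero. Classify cCR and relapse where the other four items decide them, and treat the rest as missing. Scoring every teleconsultation as missing would discard cases that can be decided.

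The cost is protocol wording, a data field for the reference scan, in-person attendance by some patients at a visit already scheduled, and a few scans that change from discretionary to compulsory.

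### From month 6, one-year cCR and time to cCR can credit the allocated drug with a response reached on both study drugs, and no stated analysis separates these responses

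*Protocol*

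**What the plan says.** Protocol section 6.3 (Treatment Phase) sets the rule for patients whose symptoms persist at T4, month 6. The dose may be raised, or the patient "will be given an addition of a second therapy, i.e. combination therapy of steroid and methotrexate may be used". The rule applies to both arms. For flares the allocated treatment is up-titrated, and after relapse it is restarted. T4 is therefore the point at which the text brings in the other arm's drug.

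The same section defines two endpoints that run past T4:

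- The cCR rate, called the primary endpoint there, is "defined as the proportion of patients who have an M-score of ≤ 1 at ≤1 years after treatment".
- The second is listed as "The time to cCR, defined as the median time to cCR post randomisation".

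Neither definition depends on the treatment received.

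Section 11.2 makes ITT the primary analysis and names one sensitivity analysis: "A Per Protocol (PP) analysis will be performed on all patients who have completed 6 months of treatment regimen as a sensitivity analysis". For time to response it states: "The secondary outcomes of time-to clinical or radiological response and time-to-relapse will be evaluated via the Kaplan-Meier method", with a log-rank test and hazard ratio.

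Section 11.2 also gives a different primary outcome: "The primary outcome of 6-month clinical or radiological complete response will be compared between arms using Chi-square test". That outcome is read at T4, before any add-on. On imaging, section 6.3 says that for patients unresolved at month 3 "a repeat breast ultrasound will be required at the 6^th^ (T_4_) month", and Figure 1 schedules no ultrasound after T4. The only scheduled visit after T4 is month 12: "The last clinical visit at the 12^th^ (T_5_) month may be a physical clinical visit or teleconsultation".

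**The concern.** The add-on is the comparator itself. A patient allocated to prednisolone who fails at month 6, receives methotrexate as well and then reaches an M-score of 0 is counted as a success of prednisolone, and the reverse holds in the other arm.

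A reader of the one-year cCR rate or the time-to-cCR hazard ratio cannot tell how many responses came on the allocated drug alone. Section 1.2c says that the trial assesses how well each drug works. After month 6 these two results instead compare starting on one drug with starting on the other, with the combination available to failures in both arms.

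If the combination works equally well in both arms, the arm with more month-6 failures gains more credited responses and both results move towards no difference. If it works unequally, or is used unequally in this open-label trial, the shift can go either way.

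**Working it through.** The protocol states no figure on this point: no design response rates, no expected add-on use and no combination response rate. The check therefore traces one patient and then works a range under stated assumptions.

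**One patient.** Baseline M-score 8; month 6 = 3 (not cCR, symptoms unresolved); combination started; month 12 = 0.

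- ITT: M-score ≤1 within one year, so she is a cCR for her allocated drug, with her event at month 12.
- Per protocol: she completed six months of the regimen, so she stays in the set with the same result.
- Six-month outcome (section 11.2): read before the add-on, so it is unaffected.

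**Inputs for the range**

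- n = 20 per arm (section 5.1).
- Six-month response p1 = 0.75 for methotrexate. Section 1.1 cites complete response of up to 75%; this is used only as an illustration.
- p2 = 0.50 for prednisolone (assumption).
- c = share of month-6 non-responders given the combination (assumption, varied).
- s = share of those reaching cCR by month 12 (assumption, 0.6 unless stated).

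**One-year cCR rate.** ITT rate = p + (1 − p)·c·s. If no up-titrated patient responds, the supportive rate, which gives no credit after the add-on, is p. The supportive difference is then 0.75 − 0.50 = 25 points.

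| c | ITT, methotrexate | ITT, prednisolone | ITT difference (points) | ITT hazard ratio |
|---|---|---|---|---|
| 0.1 | 0.765 | 0.530 | 23.5 | 1.94 |
| 0.25 | 0.7875 | 0.575 | 21.3 | 1.88 |
| 0.5 | 0.825 | 0.650 | 17.5 | 1.79 |
| 1 | 0.900 | 0.800 | 10.0 | 1.66 |

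Responses credited after the add-on at c = 0.5: 20 × 0.25 × 0.5 × 0.6 = 1.5 with methotrexate and 20 × 0.50 × 0.5 × 0.6 = 3 with prednisolone.

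**Hazard ratio.** A constant hazard to month 6 gives a true ratio of ln(0.25)/ln(0.50) = 2.0. With readings at months 1, 2, 3, 6 and 12, the large-sample Cox score equation with Efron ties gives 1.99 without add-on credit and the values in the last column with it. If responses are instead spread evenly over the visits at months 1, 2, 3 and 6, the figures at c·s = 0.3 are about 1.9 and 1.7, the same pattern.

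**Unequal add-on success, c = 0.5** (s for methotrexate v prednisolone):

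- 0.4 v 0.8: 0.80 − 0.70 = 10 points
- 0.8 v 0.4: 0.85 − 0.60 = 25 points
- 0.9 v 0.3: 0.8625 − 0.575 = 28.8 points

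The direction is therefore not fixed.

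**If up-titration also works.** Let 20% of the non-responders who are only up-titrated respond (c = 0.5, s = 0.6):

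- ITT: 0.85 − 0.70 = 15 points, hazard ratio 1.74
- Supportive: 0.775 − 0.55 = 22.5 points, hazard ratio 1.91

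Here the supportive result is no longer the six-month result.

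**Precision.** Wald 95% intervals with 20 per arm:

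- 25 points: ±1.96 × √(0.75 × 0.25/20 + 0.50 × 0.50/20) = ±29.0, so −4 to 54
- 17.5 points: ±1.96 × √(0.825 × 0.175/20 + 0.65 × 0.35/20) = ±26.7, so −9 to 44

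**The case against.** The strongest case against is that nothing here is invalid. ITT is a sound comparison of starting strategies, and the hypothesis, first objective and section 11.2 all point to a six-month outcome read before any add-on. A further sensitivity analysis is the kind of detail a SAP may hold. The six-month outcome is indeed untouched, and the point would weigh less if the protocol settled on it as its only primary. But section 6.3 calls one-year cCR primary, and the protocol itself fixes the add-on rule, both endpoint definitions and one sensitivity set that keeps these patients. An unseen SAP could add an analysis only if the add-on and its date are captured. Drug accountability might allow a reconstruction, but no section says that these items are recorded.

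A second objection is that time to cCR is defined as a median, and if more than half of an arm responds by month 6, later responses cannot move that arm's median. That is correct. The log-rank test and hazard ratio in section 11.2 still move.

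A third is size. Section 1.2a cites 94% improving on methotrexate and 80.7% responding well on steroid. These are looser outcomes than complete response, but at c·s = 0.3 they would credit only 20 × 0.06 × 0.3 = 0.4 and 20 × 0.193 × 0.3 = 1.2 patients, and the difference would go from 13.3 to 13.3 × 0.7 = 9.3 points. The effect may well be small.

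Last, the supportive analysis has its own bias. In an open-label trial (section 8.5), the clinician's choice between up-titration and add-on decides whether a later response counts. That stands, and it is why the analysis should sit beside ITT and not replace it.

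**Conclusion.** The concern holds. From month 6, the one-year cCR rate and the time-to-cCR hazard ratio credit the allocated drug with responses reached on both study drugs, and neither stated analysis set separates them.

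The size cannot be known from the protocol. Under the assumed 75% v 50% and equal add-on success of 60%, the one-year difference falls from 25 points to between 23.5 and 10 as add-on use rises from 10% to 100% of non-responders, and the hazard ratio from 1.99 to between 1.94 and 1.66. Unequal success can push the difference either way. The effect is modest if the combination is seldom used.

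The exposure is mainly one scheduled clinical reading, at month 12. Radiological response is essentially unaffected. The point should be addressed because it changes what the one-year results can be said to show. It will not change significance in a trial of 40.

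**What to change.** 1. Record the name and start date of any added study drug.
2. Keep ITT for one-year cCR and time to cCR, and describe both results as a comparison of starting strategies.
3. For these two endpoints, pre-specify a supportive analysis that counts a response first reached after the other arm's drug was added as non-response. Keep the patient in her allocated arm and in the risk set to the end of follow-up. Do not censor at the add-on, because the add-on follows non-response and such censoring would be informative.
4. Continue to credit responses after up-titration of the allocated drug.
5. Leave the six-month outcome, radiological response and the clinical rule for adding therapy as they are.

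The cost is two database fields and a short addition to sections 6.3 and 11.2. The supportive analysis does not remove the effect of aspiration or surgical drainage, which section 6.3 allows when medical therapy fails.
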